### Participants

#### Sample size

As we were unable to find any publication regarding acupuncture for CVR capacity, we could not calculate the appropriate sample size according to the sample size calculation formula. We determined an appropriate sample size of 60 for a pilot study. Both the treatment and control groups will contain 30 eligible participants. The outcomes of this study will aid in the calculation of the appropriate sample size for further randomized clinical trials.

#### Inclusion criteria

Patients of either sex are eligible for entry into this study if they meet the following inclusion criteria: (1) age between 30 and 80 years with acute cerebral infarction, with an onset time of less than 7 days, (2) confirmed as meeting the Western medicine diagnostic criteria for cerebral infarction issued by the American Heart Association/American Stroke Association (AHA/ASA) in 2015 [52], (3) confirmed as meeting the traditional Chinese medicine diagnostic criteria developed by the Stroke Diagnosis and Curative Effect Evaluation Standard (Draft) of the State Administration of Traditional Chinese Medicine, Acute Encephalopathy Research Group [53], (4) confirmation of diagnosis by head CT or MRI, (5) confirmed CVR impairment as assessed using the breath-holding-test, (6) NIHSS score within the range of 5–20 points, (7) Glasgow Coma Scale score ≥12 points, and (8) agreement to participate in this trial and signing an signed Informed Consent Form.

#### Exclusion criteria

Patients are ineligible if they meet the following exclusion criteria: (1) use of antithrombotics such as low molecular heparin for the treatment of another conditions, (2) carotid artery stent in situ, (3) severe heart, lung, or kidney disease, (4) inability to cooperate during ultrasound examination of the brain or quantitative evaluation due to another condition.

#### Discontinuation criteria

Reasons for discontinuation of treatment may include, but are not limited to, the following: (1) participant’s decision to discontinue treatment at any time for any reason, (2) investigator’s determination to discontinue treatment for the patient’s safety and best interests at any time, (3) inability to tolerate the treatment stimulation at any time during the course of the study, (4) occurrence of serious side effects during the treatment course, (5) exacerbation of the disease making it difficult for the participant to continue treatment, (6) inability of the participant to cooperate during assessment for any reason, and (7) concomitant therapy during the trial that may affect the study results.

#### Loss to follow-up

An intention-to-treat approach will be used, and reasons for which patients have been lost to follow-up must be recorded in detail and analyzed after the trial. If the number of cases lost to follow-up is within 10% of all participants, the data from these cases will not be included in the analysis. If the number of cases lost to follow-up exceeds 10%, data from the cases lost in the treatment group will be regarded as invalid, while data from the cases lost in the control group will be regarded as valid. Thus, the effective percentage of the treatment group will remain higher than that of the control group, allowing us to further analyze the efficacy of the intervention.

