### Statistical analysis

Data analysis will be performed by statisticians who are blinded to the entire allocation and intervention process. The statisticians are affiliated with the Research Center of Clinical Epidemiology at Peking University Third Hospital in Beijing, China, which is one of the most authoritative statistics centers in the country. An intention-to-treat analysis will be conducted using the SPSS statistical software package (V.22.0) (International Business Machines Corporation). Two-tailed analyses will be conducted, with the level of statistical significance defined as *P* < 0.05. Baseline characteristics, such as gender, age, NIHSS score, GCS score, previous duration, and impaired CVR, will be analyzed. The categorical data will be described as *n* (%), and continuous data using mean ± SD. If the data meets the standard of the parameter test, a chi-square test will then be conducted. Independent sample *t* tests will be used for comparisons among the groups, while paired *t* tests will be used for within-group comparisons. The efficacy of the intervention will be compared between the two groups using *χ*
^2^ analysis.

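### The loss-to-follow-up rule is not the declared intention-to-treat analysis: it deletes up to 6 lost patients, then from the 7th treats losses differently by arm, and its stated consequence contradicts it

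*Protocol article*

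**What the plan says.** All references are to the protocol article, Methods.

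- **Loss to follow-up** opens by declaring an intention-to-treat approach and then sets two rules. The first: "If the number of cases lost to follow-up is within 10% of all participants, the data from these cases will not be included", so those patients drop out of the comparison. The second applies beyond that limit: "data from the cases lost in the treatment group will be regarded as invalid, while data from the cases lost in the control group" count as valid. The section then draws the consequence that "the effective percentage of the treatment group will remain higher than that of the control group" and says this allows further analysis of efficacy.
- **Statistical analysis** repeats the label: "An intention-to-treat analysis will be conducted using the SPSS statistical software package". It assigns t tests to comparisons between and within groups and a chi-square test to efficacy. It also says: "Data analysis will be performed by statisticians who are blinded to the entire allocation and intervention process".
- **Sample size**: "We determined an appropriate sample size of 60 for a pilot study", and "Both the treatment and control groups will contain 30 eligible participants".
- **Outcome measures**: the primary outcomes, CVR and BHI, are continuous quantities computed from flow velocities.
- **Discontinuation criteria** include "inability to tolerate the treatment stimulation at any time during the course of the study", worsening of the disease, and inability to cooperate with assessment.

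The article does not define valid, invalid or effective percentage.

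**The concern.** Intention-to-treat means that every randomised patient counts in the allocated arm and that missing outcomes are handled in a way that does not favour either arm. Neither branch does this. Deleting the lost patients leaves only those who completed, and the arms stay comparable only if the losses are unrelated to outcome. Giving lost patients a status according to their arm builds a difference into the comparison that has nothing to do with the intervention. Because the method hangs on an observed count, one further loss changes how all earlier losses are handled.

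The sentence on the consequence adds a second problem. A missing-data rule should not be justified by which arm it will leave ahead, and on the most natural reading this rule moves the percentages the other way.

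At stake is the between-group comparison itself. The pilot label does not remove the problem, because the Sample size section says the results will be used to size later trials, so a distorted difference would be carried forward.

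**Working it through.** **Threshold.** 10% of 60 is 0.10 × 60 = 6. Six losses are 6/60 = 10.0%, within the limit; seven are 7/60 = 11.7%, above it. The rule therefore changes at the 7th loss.

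**Inputs.** From the documents: 30 per arm, two-sided 5% level, chi-square test for efficacy. Assumed, because the article gives none: response rates, the split of losses between arms, and losses unrelated to outcome unless stated otherwise.

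**Branch 1, up to 6 lost (deletion).** Take a true 15/30 = 50% in each arm and lose 6 treatment patients.
- All six were failures: 15/24 = 62.5%, a shift of +12.5 points.
- All six were responders: 9/24 = 37.5%, a shift of −12.5 points.
- Three lost per arm: 0 if the lost are alike in both arms; +11.1 or −11.1 if they differ completely.

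The direction is not fixed.

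**Branch 2, 7 or more lost, failure/success reading.** The shift in the difference, treatment minus control, is

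−(true responders among lost treatment + true non-responders among lost control) / 30.

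It is never positive. With 7 losses it runs from 0 to −7/30 = −23.3 points, depending on who is lost. With losses unrelated to outcome, equal true rates of 30% to 70%, and splits of 4+3, 3+4, 7+0 and 0+7 (treatment + control), it runs from −7.0 to −16.3 points; for 4+3 it is −11.0 to −12.3.

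Expected percentages:
- True 60% in both arms, 4+3 lost: (0.6 × 26)/30 = 52% against (0.6 × 27 + 3)/30 = 64%, a difference of −12 points.
- True 60% in both arms, 6+6 lost: (0.6 × 24)/30 = 48% against (0.6 × 24 + 6)/30 = 68%, a difference of −20 points.
- True 80% against 50%, 4+3 lost: (0.8 × 26)/30 = 69.3% against (0.5 × 27 + 3)/30 = 55.0%, so +14.3 of the true +30 points remain.
- True 80% against 50%, 6+6 lost: (0.8 × 24)/30 = 64% against (0.5 × 24 + 6)/30 = 60%, so +4 points remain.

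Rejection rates of the Pearson chi-square test, by exact binomial enumeration. Symmetric handling here means deleting the same losses in both arms, which is unbiased only because the losses are assumed unrelated to outcome.

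| True rates (treatment, control) | Lost (treatment + control) | Protocol rule | Symmetric handling |
|---|---|---|---|
| 60%, 60% | none | about 5% | about 5% |
| 60%, 60% | 4+3 | about 14%, almost all for control | about 5% |
| 60%, 60% | 6+6 | about 33%, almost all for control | about 5.5% |
| 80%, 50% | none | 69% for treatment | 69% |
| 80%, 50% | 4+3 | 17% for treatment | 65% |
| 80%, 50% | 6+6 | 2% for treatment | 61% |

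**Branch 2, discard/keep reading.** Suppose lost treatment patients are dropped and lost control patients kept. With a true 15/30 in each arm and 4+3 lost: 15/26 − 15/30 = +7.7 points if the lost treatment patients were failures, 11/26 − 15/30 = −7.7 if they were responders. The handling still depends on arm, but the direction is again open.

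**Against the stated consequence.** On the failure/success reading the treatment percentage can only fall or stay, and the control percentage can only rise or stay. On the discard/keep reading nothing guarantees an order. On neither reading does it follow that treatment remains higher.

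**Against the primary outcomes and the blinding.** A missing week-2 CVR or BHI has no numerical value that corresponds to valid or invalid, so branch 2 cannot feed the t tests. To apply it, someone must know which patients are in the treatment arm.

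**The case against.** The strongest reply is that the two key words are undefined and that the figures depend on one reading of them. This stands: the numerical size of branch 2 is conditional. The failure/success reading is nevertheless the more natural one beside an effective percentage, and the rule is arm-dependent on either reading.

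Second, the error rates concern a binary efficacy endpoint with assumed response rates and loss splits, not CVR or BHI. This also stands. For the primary outcomes, branch 2 is inapplicable rather than shown to be biased. The article's 20% limit for impaired CVR might serve as a responder cut-off, but the article does not tie it to the efficacy test. An analysis plan may supply a definition; it would not make the rule arm-neutral.

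Third, several stronger inferences are tempting and are not supported:
- *The bias reverses direction at the 7th loss.* What certainly changes there is the rule. Deletion has no fixed direction, and under the discard/keep reading no reversal need occur.
- *A real benefit is wiped out at the cut.* In the 80% against 50% example about 14 points remain with 4+3 lost. Only with 12 losses, a fifth of the trial, does the difference nearly vanish, and the article gives no expected loss rate.
- *Blinded statisticians could never apply the rule.* It could be applied after the code is broken or by an unblinded person. The article does not say who would do it.
- *Losses are shown to depend on arm and outcome.* The reasons listed are mainly for stopping treatment, which is not the same as being lost. A link is plausible, since the Discussion describes the treatment arm as the stronger stimulus, but it is not established.

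Finally, the article does not expressly call this the primary analysis. It offers no other handling of losses, however.

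**Conclusion.** The point holds and must be fixed before analysis. Without any assumption: the rule contradicts the declared intention-to-treat analysis, switches method at the 7th of 60 losses, handles losses by arm above that, cannot be applied to continuous CVR and BHI in its second branch, needs arm knowledge that the blinded statisticians are not to have, and is justified by a consequence that does not follow and that presupposes the result.

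The size is illustrative. For a binary endpoint on the failure/success reading, seven losses unrelated to outcome shift the difference by roughly 7 to 16 points against treatment over equal true rates of 30% to 70%. The rejection rates in the table rest on the same reading and on the assumed rates and splits. Up to six losses, the bias may go either way or be nil. These are explicit rules in the text, not detail left to an analysis plan.

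**What to change.** 1. Delete both branches of the loss rule and the sentence on the effective percentage that follows them.
2. State that all randomised patients are analysed in their allocated arm, using the week-2 assessments of patients who stopped treatment wherever these are available, and separate stopping treatment from loss to follow-up.
3. Prespecify one missing-data method, the same in both arms and whatever the loss rate. A baseline-adjusted likelihood model, or multiple imputation using arm, baseline CVR and BHI, and baseline and week-1 NIHSS and Barthel scores, would serve; with 30 per arm the choice between them is a matter of judgement.
4. Keep best-case and worst-case imputation, applied in both directions, as a labelled sensitivity analysis only, for outcomes with a defined response.
5. Continue to report numbers and reasons for loss by arm.

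The cost is wording in the protocol and analysis plan and a little extra analysis. No patients or visits are added.

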### Intervention

A bloodletting regimen, using a three-edged needle, will be performed based upon descriptions in the ancient literature and our clinical experience. The bloodletting will be performed by certified acupuncturists with at least 20 years of clinical experience. All treatment details will be standardized among practitioners who will receive relevant training and video guidance prior to the first acupuncture session. Patients will adopt a supine position during the treatment. The operators will sterilize the skin of an area of 3 cm around the acupoints with 75% alcohol. Participants in the treatment group will receive acupuncture utilizing the waking up the spirit needling method, while participants in the control group will be treated using 12-meridian hand and foot acupuncture. All treatments will be performed once a day on weekdays, followed by a 2-day rest period on weekends, for a total course of 2 weeks. Each treatment session will last approximately 35 min: the first 5 min will consist of the acupuncture procedure, following which the needles will be retained for 30 min in the patients of both the treatment and control groups.

#### Treatment group

Acupuncture utilizing the waking up the spirit needling method will be performed as follows. First, patients will adopt a supine position, then the operators will sterilize the skin of an area of 3 cm around acupoints with 75% alcohol. Acupuncture bloodletting will be conducted at acupoints *Bai Hui* (DU-20), *Si Shen Cong* (EX-HN1), and at 12 well-points using a three-edged needle which will be inserted into the skin at a depth of approximately 5–10 mm. The needle will be withdrawn immediately, and the skin around the pin hole will be squeezed to release a few drops of blood. The 12 well-points are *Shao Shang* (LU-11), *Shang Yang* (LI-1), *Li Dui* (ST-45), *Yin Bai* (SP-1), *Shao Chong* (HT-9), *Shao Ze* (SI-1), *Zhi Yin* (BL-67), *Yong Quan* (KI-1), *Zhong Chong* (PC-9), *Guan Chong* (SJ-1), *Zu Qiao Yin* (GB-44), and *Da Dun* (LR-1). Lastly, other points, such as *Ren Zhong* (GV-26), *Cheng Jiang* (CV-24), *Feng Chi* (GB-20), *He Gu* (LI-4), *Lao Gong* (PC-8), *Tai Chong* (LV-3), and *Yong Quan* (K-I1), will be chosen after the bloodletting, and the filiform needles will be inserted to depth of 10–15 mm and manually manipulated by rotation in order to produce a characteristic sensation known as “*De Qi*.” Techniques of mild reinforcing and attenuating will be applied, and the filiform needles will be retained for 30 min.

#### Control group

Twelve-meridian hand and foot acupuncture will be performed as follows. First, patients will be asked to adopt the supine position, and the operators will sterilize a 3-cm skin area around acupoints with 75% alcohol. Acupuncture including the *Qu Chi* (LI-11), *Nei Guan* (PC-6), *He Gu* (LI-4), *Yang Ling Quan* (GB-34), *Zu San Li* (ST-36), and *San Yin Jiao* (SP-6) points will be stimulated with filiform needles to a depth of 10–15 mm. The needles will be manually manipulated by rotation methods in order to produce a characteristic sensation known as *De Qi*. Techniques of mild reinforcing and attenuating will be applied, and the filiform needles will be retained for 30 min.

#### Follow-up

All participants will continue to undergo conventional therapy according to the National Clinical Guideline for Stroke [54]. Recurrence rate and Barthel Index scores will be assessed at the 3- and 6-month follow-ups for further information related to prognosis, though these will not be factored in to our assessment of the main outcomes.

### Outcome measures

#### Primary outcome measures: CVR and BHI

Cerebrovascular reserve (CVR)CVR will be calculated at baseline and 2 weeks after the first acupuncture session according to the following formula, in which the mean blood flow velocity (MFV) of the bilateral middle cerebral artery is measured using the transcranial Doppler (TCD) Breath-holding Test:$$ \begin{array}{l} CVR = \left( MFV\ \mathrm{after}\ \mathrm{breath}\hbox{-} \mathrm{holding}\ \hbox{--}\ MFV\ \mathrm{before}\ \mathrm{breath}\hbox{-} \mathrm{holding}\right)/ MFV\ \mathrm{before}\\ {}\ \mathrm{breath}\hbox{-} \mathrm{holding} \times 100\%.\end{array} $$
CVR function is considered impaired if the calculated CVR is less than 20%.CVR will be accessed via the TCD breath-holding test. For this test, patients are instructed to practice holding their breath at least twice prior to assessment. Patients then adopt the supine position and are asked to breathe normally for 5 min. Two ultrasonic probes are then placed on the bilateral temporal window and connected to the EMS-9 W TCD machine (Nanjing Bangao Company, Nanjing, China). The ultrasonic probe is used to record at a depth of roughly 50–55 mm, measuring blood velocity in the bilateral middle cerebral artery (M1). Once an adequate signal has been obtained, the probes are fixed, and the MFV is recorded while the patient is in a calm state. The patient is then asked to hold their breath for at least 15 s, following which the MFV is re-recorded.Breath-holding Index (BHI)BHI assessments will be conducted at baseline and 2 weeks after the first acupuncture session according to the following formula, in which the MFV of the bilateral middle cerebral artery is measured using the TCD breath-holding test:$$ \begin{array}{l} BHI = \left( MFV\ \mathrm{after}\ \mathrm{breath}\hbox{-} \mathrm{holding}\ \hbox{--}\ MFV\ \mathrm{before}\ \mathrm{breath}\hbox{-} \mathrm{holding}\right)/ MFV\ \mathrm{before}\ \\ {}\mathrm{breath}\hbox{-} \mathrm{holding} \times \left(100/\mathrm{time}\ \mathrm{holding}\ \mathrm{breath}\right).\end{array} $$

#### Secondary outcome measures: NIHSS and Barthel Index scores

NIHSS [55]Neurological function will be assessed using the National Institutes of Health Stroke Scale (NIHSS) at baseline, 1 week after the first acupuncture treatment, and 2 weeks after the first acupuncture treatment. The NIHSS is widely used for assessing neurological function defect symptoms.Barthel Index [56]Functional ability will be assessed using the Barthel Index at baseline, 1 week after the first acupuncture treatment, and 2 weeks after the first acupuncture treatment.The Barthel Index is widely used for assessing quality of life of clinical patients.

#### Adverse events

Adverse events (AEs) are defined as negative or unintended clinical manifestations following the treatment [57]. Our investigators will collect information regarding AEs every 3 days. Participants will be instructed to report any abnormal reactions or uncomfortable feelings experienced to any researcher. All related and unexpected AEs will be recorded on Case Report Forms (CRFs) in detail, including time of occurrence, degree of AE, and possible causes. Patients with mild and moderate AEs will be treated for their symptoms and closely monitored as necessary by the researcher. Severe AEs will be reported to the Research Ethics Committee, which will provide medical advice to the research team within 48 h, and the Research Ethics Committee will determine whether the patient is eligible for further treatment associated with the study.

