**Fig. 1 Fig1:**
[figure not shown]
Flow chart

**Table 1 Tab1:** Time table

	Baseline (before treatment)	Treatment			Follow-up and data collection
		Week 0	Week 1	Week 2	Data collection and analysis
Patients entered					
Medical history	√				
GCS	√				
CVR	√				
Sign the informed consent	√				
Randomization	√				
Intervention		√	√	√	
Outcomes					
Primary outcomes					
CVR		√		√	
BHI		√		√	
Secondary outcome					
NIHSS		√	√	√	
Barthel Index		√	√	√	
Adverse events	√	√	√	√	√
Data collection					√

*GCS* Glasgow Coma Scale, *CVR* cerebrovascular reserve, *BHI* Breath-holding Index, *NIHSS* National Institutes of Health Stroke Scale

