## Discussion

This trial aims to investigate whether acupuncture utilizing the waking up the spirit needling method can improve CVR capacity in patients with acute cerebral infarction, thus reducing NIHSS scores and preventing further disease progression. Some studies [60–62] have demonstrated that acupuncture may improve symptoms in patients with cerebral infarction and, according to clinical observations, acupuncture utilizing the waking up the spirit needling method may produce similar effects. Furthermore, increased focus has been directed at the relationship between CVR and cerebral infarction [32]. Acupuncture is widely utilized in the treatment of cerebral infarction, though the mechanisms underlying its effects remain unclear. In this randomized, controlled study we expect that participants will experience pain relief as well as improved function and strength. Furthermore, data and evidence gained from this study will be utilized in the development of future research projects regarding the effects of acupuncture in patients with acute cerebral infarction.

The risks of taking part in this trial are minimal. Acupuncture is a very safe treatment when conducted by properly trained clinicians. Occasionally, acupuncture can make people feel nauseous, faint, or experience a temporary increase in pain either during or after treatment.

The global outlook for cerebral infarction is not good [4, 63], and both first- and second-level prevention are critical at reducing the impact of this potentially life-threatening and devastating condition [63–70]. CVR is an independent risk factor for the occurrence [18–21], progression [22–25], and recurrence [26] of cerebral infarction that requires attention. Some researchers have even proposed that CVR should be assessed regularly, as one of the key targets for prevention [71].

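### Active adverse event enquiry every 3 days is sparse for brief reactions around 10 weekday sessions, and the adverse event definition does not fit the baseline collection in Table 1

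*Protocol article*

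**What the plan says.** The Adverse events section under Outcome measures gives the definition: "Adverse events (AEs) are defined as negative or unintended clinical manifestations following the treatment". It then sets two routes of collection. The active route is "Our investigators will collect information regarding AEs every 3 days". The passive route follows directly: "Participants will be instructed to report any abnormal reactions or uncomfortable feelings experienced to any researcher". For events entered on the case report form, the section asks for the time of occurrence, the degree and possible causes.

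The Intervention section gives one session per weekday for 2 weeks, about 35 minutes each. The Discussion names the expected reactions: "Occasionally, acupuncture can make people feel nauseous, faint, or experience a temporary increase in pain either during or after treatment".

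In Table 1, the row "Adverse events" is ticked in all five columns, including the one headed as baseline, before treatment. The CVR row is ticked in that column too. The primary outcome section says that CVR is measured by the transcranial Doppler breath-holding test, at baseline and 2 weeks after the first session.

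**The concern.** There are two separate issues.

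The first is the match between the enquiry interval and the expected harms. Nausea, faintness and a passing increase in pain are short-lived and tied to a session. A planned question every third day can come after such a reaction has resolved, and capture then depends on the patient volunteering or recalling it. Eligibility extends to an NIHSS score of 20 and to "Glasgow Coma Scale score ≥12 points", so some patients may volunteer less readily than others. This trial compares a stronger stimulus, including bloodletting, with a milder one, and its results are meant to inform later trials. A thin record of mild reactions weakens that use.

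The second is the collection window. The definition starts at treatment, whereas Table 1 starts before it. The trial's own baseline procedure, a breath-hold of at least 15 s after at least two practice holds in patients within 7 days of infarction, falls in the gap. Two investigators could handle the same baseline event differently, and each could cite the article in support.

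**Working it through.** **Enquiries against sessions.** The plan states no count of enquiries, so there is no figure to reproduce. The inputs are one session per weekday for 2 weeks (Intervention) and an enquiry every 3 days (Adverse events).

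Sessions: 5 weekdays × 2 weeks = 10 in any 14-day window, whatever weekday treatment starts.

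Enquiries in days 1 to 14, by the day on which the 3-day cycle begins:
- from day 1: days 1, 4, 7, 10, 13 = 5
- from day 2: days 2, 5, 8, 11, 14 = 5
- from day 3: days 3, 6, 9, 12 = 4

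For a Monday start, sessions fall on days 1–5 and 8–12. Sessions with an enquiry on the same day:
- cycle from day 1: days 1, 4, 10 = 3 of 10
- cycle from day 2: days 2, 5, 8, 11 = 4 of 10
- cycle from day 3: days 3, 9, 12 = 3 of 10

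So 6 or 7 of the 10 sessions have no enquiry on the day.

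I checked all five weekday starts with all three cycle positions (15 combinations). The longest gap from a session to the next enquiry is 2 days if a same-day enquiry counts, and 3 days if it does not, for example because it took place before that day's session. In 8 of the 15 combinations the last one or two sessions come after the final enquiry inside the 14 days. These are covered only if the round continues, or by the follow-up collection ticked in Table 1.

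**Size of any under-count.** Take the Monday start with the cycle from day 3, and suppose reactions are spread evenly over sessions. Let p be the share of reactions on non-enquiry days that are neither volunteered nor recalled. The share lost is then 7 × p / 10 = 0.7p. The article contains nothing from which to set p, and open reporting could make it small. No percentage follows.

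**Effect on the arm comparison.** Let the true reaction rates be a and b, and let the same share q be lost in both arms. The observed difference is (1 − q)(a − b), which is smaller than the true one. The observed ratio is (1 − q)a / [(1 − q)b] = a/b, which is unchanged. The article gives neither a, b nor q, and does not say whether q is equal in the two arms.

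**Definition against timetable.**

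| Event | Collected under Table 1? | Adverse event by the definition? |
|---|---|---|
| At the baseline breath-hold test | Yes (baseline column) | No, it precedes treatment |
| During or after a session | Yes | Yes |
| At the week-2 breath-hold test | Yes | Yes, it follows treatment |

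The two statements disagree in the first row and nowhere else.

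**The case against.** The strongest reply is that the 3-day round is not the sole route. Participants are told to report any reaction to any researcher. The Data management section counts therapists among the researchers, and a therapist is with the patient every weekday, so each session already offers a chance to report. Patients must also be able to cooperate with the ultrasound examination, hold their breath on instruction and sign consent, so the NIHSS and Glasgow limits on their own overstate how many cannot report. All of this stands, and it is why the claim is possible under-counting of mild reactions and not loss of events. What remains is that no planned question is tied to the session, where the named reactions occur. Recording the time of occurrence helps to place an event once it is known, but does nothing for one that was never raised.

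A reader might infer three stronger things that the article does not support:
- **That session reactions will be missed or cannot be counted.** They follow treatment, so they meet the definition, and recorded events carry a time.
- **That the 3-day round contradicts the discontinuation criteria**, such as "inability to tolerate the treatment stimulation at any time during the course of the study". Those criteria rest on the participant's or investigator's decision, or on what is seen at the time. None is tied to the round.
- **That bloodletting will look safer than it is by some stated amount.** That needs reaction rates by arm and a recall rate, and the article has neither.

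It can also be said that per-session checklists belong in the case report form or full protocol. That is fair as to omissions. Here, however, the article does fix the interval, and a better one is available at almost no cost.

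**Conclusion.** The point holds as a modest, cheap improvement plus one inconsistency to reconcile.

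Active enquiry is set at 4 or 5 contacts for 10 sessions, with a gap of at most 2 days to the next contact (3 if a same-day contact does not count). Mild, brief session reactions may be under-counted as a result. That conclusion assumes that some such reactions are neither volunteered nor recalled at the next enquiry. Neither the amount nor any direction of bias between the arms can be derived from the article.

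The definition and Table 1 disagree about the period before treatment. The consequence is confined to baseline events, notably at the baseline breath-hold test. The week-2 test is unaffected. Table 1 shows that baseline collection is intended, so this is a wording conflict and not a demonstrated loss of data.

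Neither issue touches the primary outcomes, CVR and BHI.

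**What to change.** 1. At each of the 10 existing sessions, ask a short scripted set of adverse event questions, word for word the same in both arms, and record the answers even when there is nothing to report. Keep the 3-day investigator enquiry as the review step.
2. Reconcile the definition with Table 1: state that collection runs from informed consent and covers trial procedures, including the breath-hold test, as well as the acupuncture sessions. The Recruitment section already places consent before the baseline assessments, so the window would include the baseline test.
3. Trial status reports that about six patients had consented and been assessed at baseline, with no intervention yet given. Check that their baseline events were recorded under the reworded definition.

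The cost is one line per session on the treatment record and an edit to the definition. It needs no extra visit or staff, since someone is already with the patient for about 35 minutes. The downside is that session staff know the allocation and could probe unevenly. Hence the fixed script, with causality judged by the investigator and not by the person giving the treatment.
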